#### *Ethics and dissemination*

|                   |           |                                                                                           |    |
|-------------------|-----------|-------------------------------------------------------------------------------------------|----|
| Research approval | ethics 24 | Plans for seeking research ethics committee/institutional review board (REC/IRB) approval | 57 |
|-------------------|-----------|-------------------------------------------------------------------------------------------|----|

|                               |     |                                                                                                                                                                                                                                                                                     |    |
|-------------------------------|-----|-------------------------------------------------------------------------------------------------------------------------------------------------------------------------------------------------------------------------------------------------------------------------------------|----|
| Protocol amendments           | 25  | Plans for communicating important protocol modifications (eg, changes to eligibility criteria, outcomes, analyses) to relevant parties (eg, investigators, REC/IRBs, trial participants, trial registries, journals, regulators)                                                    | 57 |
| Consent or assent             | 26a | Who will obtain informed consent or assent from potential trial participants or authorised surrogates, and how (see Item 32)                                                                                                                                                        | 57 |
|                               | 26b | Additional consent provisions for collection and use of participant data and biological specimens in ancillary studies, if applicable                                                                                                                                               | 58 |
| Confidentiality               | 27  | How personal information about potential and enrolled participants will be collected, shared, and maintained in order to protect confidentiality before, during, and after the trial                                                                                                | 58 |
| Declaration of interests      | 28  | Financial and other competing interests for principal investigators for the overall trial and each study site                                                                                                                                                                       | 59 |
| Access to data                | 29  | Statement of who will have access to the final trial dataset, and disclosure of contractual agreements that limit such access for investigators                                                                                                                                     | 59 |
| Ancillary and post-trial care | 30  | Provisions, if any, for ancillary and post-trial care, and for compensation to those who suffer harm from trial participation                                                                                                                                                       | 61 |
| Dissemination policy          | 31a | Plans for investigators and sponsor to communicate trial results to participants, healthcare professionals, the public, and other relevant groups (eg, via publication, reporting in results databases, or other data sharing arrangements), including any publication restrictions | 62 |
|                               | 31b | Authorship eligibility guidelines and any intended use of professional writers                                                                                                                                                                                                      | 63 |
|                               | 31c | Plans, if any, for granting public access to the full protocol, participant-level dataset, and statistical code                                                                                                                                                                     | 64 |
| Appendices             |     |                                                                                                                                                                                                                                                                                     |    |
| Informed consent materials    | 32  | Model consent form and other related documentation given to participants and authorised surrogates                                                                                                                                                                                  | 72 |
| Biological specimens          | 33  | Plans for collection, laboratory evaluation, and storage of biological specimens for genetic or molecular analysis in the current trial and for future use in ancillary studies, if applicable                                                                                      | NA |

## 16.8. APPENDIX VIII. EURARTESIM PACKAGE INSERT

### PACKAGE LEAFLET: INFORMATION FOR THE USER

**Eurartesim 320 mg/40 mg film-coated tablets**  
Piperaquine tetraphosphate/dihydroartemisinin

**Read all of this leaflet carefully before you start using this medicine**

- Keep this leaflet. You may need to read it again.
- If you have any further questions, ask your doctor or pharmacist.
- This medicine has been prescribed for you. Do not pass it on to others. It may harm them, even if their symptoms are the same as yours.
- If any of the side effects gets serious, or if you notice any side effects not listed in this leaflet, please tell your doctor or pharmacist.

**In this leaflet:**

1. What Eurartesim is and what it is used for
2. Before you or your child takes Eurartesim
3. How to take Eurartesim
4. Possible side effects
5. How to store Eurartesim
6. Further information

#### 1. WHAT EURARTESIM IS AND WHAT IT IS USED FOR

Eurartesim contains the ingredients piperaquine tetraphosphate and dihydroartemisinin. It is used to treat uncomplicated malaria when use of a medicine given by mouth is appropriate.

Malaria is caused by infection with a parasite called *Plasmodium*, spread by the bite of an infected mosquito. There are different types of *Plasmodium* parasite. Eurartesim kills the *Plasmodium falciparum* parasite.

The medicine can be taken by adults, children and infants over 6 months old who weigh 5 kilograms or more.

#### 2. BEFORE YOU OR YOUR CHILD TAKE EURARTESIM

**Do not take Eurartesim if you or your child:**

- is allergic (hypersensitive) to the active substances, piperaquine tetraphosphate or dihydroartemisinin, or to any of the other ingredients of Eurartesim (see section 6 for a list of these);
- has a severe type of malaria infection which has affected parts of your body such as the brain, lungs or kidneys;
- has a heart condition, such as changes to the rhythm or rate of your heart beat, or heart disease;
- knows that any member of your family (parents, grandparents, brothers or sisters) died suddenly due to a heart problem or was born with heart problems;
- suffers from changes to the levels of salts in your body (electrolyte imbalances);
- is taking other medicines that can have an effect on heart rhythm, such as:
  - quinidine, disopyramide, procainamide, amiodarone, dofetilide, ibutilide, hydroquinidine or sotalol;
  - medicines used to treat depression;
  - medicines used to treat mental health problems such as phenothiazines, sertindole, sultopride, chlorpromazine, haloperidol, mesoridazine, pimozide, or thioridazine;

- medicines used to treat infections. These include some of the types of medicines used to treat bacterial infections (macrolides [such as erythromycin or clarithromycin] and fluoroquinolones [such as moxifloxacin and sparflaxacin]) or fungal infections (including fluconazole and imidazole) as well as pentamidine (used to treat a specific type of pneumonia) and saquinavir (for treatment of HIV);
- antihistamines used to treat allergies or inflammation such as terfenadine, astemizole or mizolastine;
- certain medicines used to treat stomach problems such as cisapride, domperidone or droperidol;
- other medicines such as vinca alkaloids and arsenic trioxide (used to treat certain cancers), bepridil (used to treat angina), diphemanil (used to treat stomach disturbances), levomethadyl and methadone (used to treat drug addiction), and probucol (used to treat high blood cholesterol levels).
- has recently (for example within about one month) been treated for malaria with certain medicines or has taken certain medicines to prevent malaria. These medicines include: mefloquine, halofantrine, lumefantrine, chloroquine or quinine

If any of the above applies to you or your child or if you are unsure, tell your doctor or pharmacist before taking or giving Eurartesim.

#### Take special care with Eurartesim

Check with your doctor or pharmacist before taking this medicine if you or your child:

- has liver or kidney problems;
- has a malaria infection caused by a parasite other than *Plasmodium falciparum*;
- is taking or has taken any other medicines for the treatment of malaria (other than those mentioned above);
- is pregnant or breastfeeding (see below);
- is female, elderly (over 65 years) or vomiting;
- is taking certain other medicines which could cause possible metabolic interactions. Examples are listed in the section "Taking other medicines".

If you are not sure about any of the above, please ask your doctor or pharmacist.

#### Use in children

Do not give this medicine to infants under 6 months or below 5 kg in weight.

#### Taking other medicines

Please tell your doctor or pharmacist if you or your child is taking or has recently taken any other medicines, including medicines obtained without a prescription. Some medicines can affect the way Eurartesim works and your doctor may decide that Eurartesim is not suitable or that extra checks are needed while you or your child is taking the medicinal products which could cause possible interactions. Examples are listed below (but there are several others):

- some medicines used to treat high cholesterol in the blood (such as atorvastatin, lovastatin, simvastatin);
- medicines used to treat hypertension and heart problems (such as diltiazem, nifedipine, nitrendipine, verapamil, felodipine, amlodipine);
- some medicines used to treat HIV (antiretroviral medicinal products): protease inhibitors (such as amprenavir, atazanavir, indinavir, nelfinavir, ritonavir), non-nucleoside reverse transcriptase inhibitors (such as efavirenz, nevirapine);
- some medicines used to treat microbial infections (such as telithromycin, rifampicin, dapsone);
- medicines used to help you fall asleep: benzodiazepines (such as midazolam, triazolam, diazepam, alprazolam), zaleplon, zolpidem;
- medicines used to prevent/treat epileptic seizures: barbiturates (such as phenobarbital), carbamazepine or phenytoin;
- medicines used after organ transplantation and in autoimmune diseases (such as cyclosporin, tacrolimus);

- sex hormones, including those contained in hormonal contraceptives (such as gestodene, progesterone, estradiol), testosterone;
- glucocorticoids (hydrocortisone, dexamethasone);
- omeprazole (used to treat diseases related to gastric acid production);
- paracetamol (used to treat pain and fever);
- theophylline (used to improve bronchial air flow);
- nefazodone (used to treat depression);
- aprepitant (used to treat nausea);
- some gases (such as enflurane, halothane and isoflurane) used to give a general anaesthetic.

#### **Taking Eurartesim without food and drink**

You should take Eurartesim tablets with water only.

You should take this medicine on an empty stomach. You should take each dose no less than 3 hours after the last food intake, and no food should be taken within 3 hours after each dose of Eurartesim. You can drink water at any time. You should not take Eurartesim with grapefruit juice due to possible interactions.

#### **Pregnancy and breast-feeding**

Tell your doctor if you are pregnant, think you may be pregnant or become pregnant, or if you are breast-feeding.

Eurartesim must not be used in pregnancy if your doctor can give you an alternative medicine. If you receive Eurartesim while pregnant, please note that a pregnancy registry is in place to monitor the pregnancy outcomes.

You should not breast-feed your baby while taking this medicine.

If you are taking folate supplements to prevent possible neural tube birth defects, you can continue taking them at the same time as Eurartesim.

Ask your doctor or pharmacist for advice before taking any medicine during pregnancy or breast-feeding.

#### **Driving and using machines**

You can drive or use machines after taking Eurartesim.

### **3. HOW TO TAKE EURARTESIM**

Always take Eurartesim exactly as your doctor has told you to. You should check with your doctor or pharmacist if you are not sure.

Take this medicine with water and on an empty stomach. You or your child should take each dose at least 3 hours after your last meal. You should also avoid eating until 3 hours after taking Eurartesim. You can drink water at any time.

If the tablets are difficult to swallow, you can crush and mix them with water; drink the mixture immediately.

A course of Eurartesim lasts 3 consecutive days. Take one dose on each day. You should try to take the dose at about the same time on each of the three days.

The daily dose depends on the patient's **body weight**. Your doctor should have prescribed a dose that is appropriate for your weight or your child's weight as follows:

| Body weight (kg)   | Daily dose (mg)                  | Total number of tablets for treatment |
|--------------------|----------------------------------|---------------------------------------|
| 5 to less than 7   | Half 160 mg/20 mg tablet a day   | 1.5 tablet                            |
| 7 to less than 13  | One 160 mg/20 mg tablet a day    | 3 tablets                             |
| 13 to less than 24 | One 320 mg/40 mg tablet a day    | 3 tablets                             |
| 24 to less than 36 | Two 320 mg/40 mg tablets a day   | 6 tablets                             |
| 36 to less than 75 | Three 320 mg/40 mg tablets a day | 9 tablets                             |
| 75 to 100          | Four 320 mg/40 mg tablets a day  | 12 tablets                            |

If you weigh more than 100 kg then follow the dose that your doctor has prescribed.

#### **Vomiting when taking this medicine**

If this happens within:

- 30 minutes of taking Eurartesim, the whole dose must be taken again.
- 31-60 minutes, half the dose must be taken again.

If you or your child vomit also the second dose, do not take or give your child another dose. Contact your doctor urgently to obtain an alternative treatment for malaria.

#### **Taking this medicine, if the malaria infection returns**

- If you or your child gets another attack of malaria you may take a second course of Eurartesim within one year if your doctor thinks this is a suitable treatment. You or your child must not take more than two courses within one year. If this happens, talk to your doctor. You or your child should not take a second course of Eurartesim within 2 months of the first course.
- If you or your child is infected more than twice in a year, your doctor will prescribe an alternative treatment.

#### **If you or your child takes more Eurartesim tablets than you should**

If you or your child takes more than the recommended dose, tell your doctor. Your doctor may suggest special monitoring for you or your child because doses higher than those recommended may have an unwanted, severe effect on your heart (see also section 4).

#### **If you or your child forgets to take Eurartesim**

If you or your child forgets to take the second dose of Eurartesim at the right time, take it as soon as you remember. Then take the third (last) dose approximately 24 hours after the second dose. If you or your child forgets to take the third (last) dose at the right time, take it as soon as you remember.

Never take more than one dose on the same day to make up for a missed dose.

Check with your doctor or pharmacist if you are not sure.

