#### 8.5.2.5. Dihydroartemisinin-piperaquine administration

The first dose will be administered crushed and dissolved in water in the clinic or the home of the participant under direct observation. The remaining two doses will be given to take at home during the following two consecutive days. Participant's caretakers will be advised to give the drug to the child at about the same time each day with water. Should a caretaker forget to give the drug dose at the set time, they will be advised to take it as soon as this is realised and to continue the recommended regimen until the dose is completed.

Participants who take DP or placebo in the clinic will be observed for at least 60 minutes. Should a participant vomit within 30 minutes of receiving the treatment drug, the full dose will be re-administered. Should a participant vomit within 30-60 minutes of drug intake, half dose will be re-administered. Repeat dosing will be attempted once and if the second dose is vomited, the participant will receive artemether-lumefantrine. Caretakers will be instructed to inform the study team the same day for a replacement dose if a participant vomits the treatment at home

To minimise QTc prolongation, Sigma Tau, Italy, the manufacturer of this brand of DP (Eurartesim®), advises patients to take the first day's dose approximately three hours after meals as fatty food can increase the absorption of piperaquine. However, overall studies show that DP when given at the

standard dose over 3 days is well tolerated and can be given safely with small amount of food, such as a biscuit.

Recently a review was completed for WHO to evaluate the safety of DP when used for IPT. Across all studies, including 7 trials, monthly DP was associated with a significantly lower risk of SAEs compared to placebo, daily trimethoprim-sulfamethoxazole, or monthly SP. Overall 12 deaths were reported among those exposed to DP and 16 among those exposed to comparator therapies, with no studies reporting any sudden or unexplained deaths.

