### *8.5.6. Adherence to study intervention protocol and strategies for retention*

#### **8.5.6.1. Adherence to study protocol and medication**

At 2, 6 and 10 weeks children will be visited at home or asked to come to the clinic to receive the PMC with DP or placebo. For the home-treatment courses, drug administration of the first daily dose will be given by a study staff or home visitor under direct supervision (day 0). The study staff will instruct the mother to administer the second and third dose around the same time the next two days (days 1 and 2). Care takers of study participants and home visitors will also be reminded through mobile phone contact to take the assigned tablets for the second and third dose. On the last day, some caretakers will be revisited at home by spot checks and asked whether and when the second and third dose was administered. All information will be recorded on the appropriate sections of the CRF.

Subjects judged to be non-compliant may continue in the study but should be counselled on the importance of taking their study medication as prescribed.

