## 9.6. SAFETY MONITORING AND REPORTING

### 9.6.1. Cardiac Monitoring

To assess the impact of monthly dosing with DP on QTc prolongation, a sub-group of 66 children (33 in each arm) will be selected to participate in cardiac monitoring sub-study at the beginning of the trial using convenience sampling. Separate written informed consent will be sought for inclusion in this sub-study.

A baseline ECGs will be done prior to the start of the first dose of the first course of DP at 2 weeks post-discharge, and again 2 days later, 4-6 hours after the 3rd dose of DP, and before each

subsequent first dose and after each subsequent 3rd dose of each next course (i.e. about 6 ECGs assessments in total per child). Each ECG will be taken in triplicate. Information on food intake and co-medication will be collected by questionnaire. A 200 micro litre blood sample will be taken for piperazine drug levels at the same time that the ECGs are taken. Piperazine levels will be measured in a specialised laboratory from the Mahidol Oxford Tropical Medicine Research Unit (MORU), in Bangkok, Thailand which is one of the few laboratories globally that have this capacity.

ECGs will be read on site by trained local staff, and forwarded electronically to Makerere University and KEMRI Kisumu for quality control. All abnormal ECGs (see grading below) and a sub-set of other ECGs will be read by a Paediatric Cardiologist fellow. QT intervals will be adjusted for heart rate prior to subsequent analysis using the Fridericia formula ( $QT_c = QT \text{ times the cube-root of the RR interval on the ECG}$ ).

All ECGs will be graded based on the  $QT_c$  interval as mild, moderate, severe and potentially life threatening as per international guidelines from the National Institute of Health (NIH): Division of AIDS (DAIDS) Table for Grading the Severity of Adult and Pediatric Adverse Events.

- Grade 1 (mild): Asymptomatic,  $QT_c$  interval 450 –470 ms
- Grade 2 (moderate): Asymptomatic,  $QT_c$  interval 470-500 ms
- Grade 3 (severe): Asymptomatic,  $QT_c$  interval >500 ms OR  $\geq 60$  ms above baseline (pre-course level)
- Grade 4 (potentially life threatening): Life-threatening consequences, e.g. Torsade de pointes or other associated serious ventricular dysrhythmias

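### The forgotten-dose rule for home DP doses sets no spacing and no daily limit, so a late second dose can fall on the same day as the third, which the appended leaflet advises against

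*Protocol*

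**What the plan says.** Section 8.5.2.5 has the first dose of each course given under observation and the other two handed to the family: "The remaining two doses will be given to take at home during the following two consecutive days". Caretakers are to "give the drug to the child at about the same time each day with water". If a dose is forgotten, "they will be advised to take it as soon as this is realised and to continue the recommended regimen until the dose is completed".

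Section 8.5.6.1 repeats the timing: "The study staff will instruct the mother to administer the second and third dose around the same time the next two days". It adds phone reminders for those two doses and a home spot check of some caretakers on the last day. It has no forgotten-dose rule.

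The package leaflet in Appendix VIII (section 16.8) also has a forgotten second dose taken when remembered, but goes on to set two limits. The first is spacing: "Then take the third (last) dose approximately 24 hours after the second dose". The second is a daily cap: "Never take more than one dose on the same day to make up for a missed dose". For a forgotten third dose it says only to take it when remembered.

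On vomiting, section 8.5.2.5 gives a full repeat within 30 minutes, a half repeat from 30 to 60 minutes, and one repeat attempt. A separate sentence covers the home: "Caretakers will be instructed to inform the study team the same day for a replacement dose if a participant vomits the treatment at home". That sentence has no time window of its own.

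**The concern.** The protocol's forgotten-dose rule starts the way the leaflet's does but stops before either limit. A caretaker who finds on the third day that the second dose was missed is told to give it now and continue. The rest of the instruction says that the third dose belongs to that day at the usual hour. Followed literally, both are given on one day, against the limit in the protocol's own appendix.

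The protocol does not treat this as trivial. Section 11.8.1.2 describes piperaquine's QTc prolongation as dose-dependent and as the main safety concern with the drug. The leaflet's section on taking too many tablets warns of a possible severe effect on the heart above the recommended dose. The rule governs doses that lay caretakers hold at home and that mostly go unobserved: section 8.2.3 requires observation only of the first dose of each course and supervises the others where feasible.

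**Working it through.** The plan states no figure on this point, so the check compares texts and adds simple arithmetic.

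**Which doses can conflict**
- First dose of a course: given under observation, so not subject to a caretaker's missed-dose rule.
- Second dose: protocol and leaflet agree on giving it when remembered. They part on what follows. The leaflet moves the third dose and caps the day at one dose; the protocol does neither.
- Third dose: both texts say to give it when remembered, and no further dose follows in that course. There is no conflict.

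Only a late second dose matters.

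**Spacing.** Let the second dose be d hours late and the third stay at its set time. The set times are 24 hours apart, so the gap is 24 - d hours:
- d = 6: 24 - 6 = 18 hours
- d = 12: 24 - 12 = 12 hours
- d = 18: 24 - 18 = 6 hours
- d = 24: 24 - 24 = 0 hours

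The leaflet keeps the gap at about 24 hours throughout. A delay made good on the second day shortens the gap without putting two doses on one day. A delay that runs into the third day does both.

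**How many doses are exposed.** Section 8.8.1.1 has 520 children per arm, and each has three courses with one second dose per course: 520 x 3 = 1560 second doses in the DP arm. This is a ceiling: every child receives every course and every second dose is given by a caretaker. The documents give no rate of forgotten doses. Doubling also requires that the dose be remembered on the day when the third is due.

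**Size of a doubled day.** Piperaquine per dose from Table 4, divided by the upper and lower edges of each weight band (the upper edges are limits not quite reached):
- 5 to <8 kg: 160/8 = 20.0 to 160/5 = 32.0 mg/kg; doubled 40.0 to 64.0
- 8 to <11 kg: 240/11 = 21.8 to 240/8 = 30.0; doubled 43.6 to 60.0
- 11 to <17 kg: 320/17 = 18.8 to 320/11 = 29.1; doubled 37.6 to 58.2
- 17 to <25 kg: 480/25 = 19.2 to 480/17 = 28.2; doubled 38.4 to 56.5

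Across these four bands the range is 37.6 to 64.0, or about 38 to 64 mg/kg. The top band (25 to <36 kg) would give 35.6 to 51.2. I leave it out of the summary on the assumption that few children under five weigh that much.

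**The case against.** The best reply is that the protocol never tells anyone to give two doses on one day. Its regimen is one daily dose on consecutive days, and continuing it can be read as moving the third dose to the next day. This stands to the extent that the double dose is an ambiguity, not an instruction. It does not remove the conflict, because the same text ties the third dose to a particular day and hour and nothing says that it moves.

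A second reply is that the leaflet is appended and so supplies the limits. But 8.5.2.5 does not refer to it for missed doses. The protocol also departs from it elsewhere, for example in the weight bands (Table 4) and in the number and spacing of courses (8.5.2.1). Staff cannot tell which of its conditions apply.

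Third, there are safeguards: separate containers for each dose (8.5.3.1), labels that may carry directions (8.5.3.2), phone reminders, and supervision or verification where feasible (8.2.3). These make the event less likely, but none states the missing rule. The participant information sheets were not in the text available, so wording there cannot be ruled out.

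Four stronger readings might be inferred and are not supported:
- That the leaflet forbids any repeat after 60 minutes. It is silent beyond 60 minutes.
- That the vomiting rule lets a caretaker double-dose. Section 8.5.2.5 carries the 30 and 30 to 60 minute windows and routes home replacement through the study team. The leaflet's daily cap concerns missed doses, and the leaflet itself has a whole dose repeated after early vomiting.
- That the QTc measurement would be mistimed. Section 9.6.1 does say "and again 2 days later, 4-6 hours after the" third dose, but the outcome in 8.6.4 is tied to the third dose with no fixed day.
- That all 520 x 6 = 3120 home doses are exposed. Half of these are third doses, for which the two texts agree.

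**Conclusion.** The point holds for a late second dose. On that one event the protocol's rule and its own appendix lead to different actions, and the protocol's wording leaves room for two full doses on one day. At most 1560 DP-arm doses could fall under the conflict; the number that would is unknown. A doubled day would be about 38 to 64 mg/kg piperaquine below 25 kg, assuming full Table 4 doses and both retained. This is a wording conflict that should be corrected because the doses are mostly unobserved and the drug's cardiac effect is dose-dependent. It is not evidence that children would be overdosed. On vomiting, all that remains is that the home-replacement sentence does not say whether the stated windows govern it.

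**What to change.** Reconcile sections 8.5.2.5 and 8.5.6.1 with the forgotten-dose section of the Appendix VIII leaflet, so that the caretaker instruction and the phone reminder carry one unambiguous rule for a late second dose, including what happens to the third. Its content is for the sponsor's clinicians; if the protocol is meant to differ from the leaflet, it should say so. In the same edit, state whether the 30 and 30 to 60 minute windows in 8.5.2.5 also apply to a replacement dose for a child who vomits at home.

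The cost is a few sentences in the protocol and matching wording in the caretaker instruction and reminder. No design, sample size or analysis changes.
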